### Physical assessment

Quantified Y Balance Test is a modification of the Star Excursion Balance Test.^37^ A detailed testing protocol has previously published.^24^ Participants position themselves on a platform with hands firmly on their hips. They are instructed to use their non-stance leg to slide a box forward as far as possible with their foot and return to the starting upright position in three defined directions (anterior, posteromedial and posterolateral). Reach distances are recorded to the nearest 0.5 cm. Individuals complete three practice trials, followed by three recorded trials in a randomised order. A failed attempt is noted when any of the following errors occurred: touching of the foot down on the floor before returning to the starting position; placing the foot on top of the sliding box for balance; and flicking or kicking the sliding box for a better performance or any loss of balance.^38^ If an individual meets any of the failure criteria, the reach attempt will be discarded and repeated. During all tests, an inertial sensor (Shimmer3; Shimmer Sensing) is mounted at the level of the fourth lumbar vertebra and secured with a custom-made elastic belt to closely match the acceleration of the body’s centre of mass during the Y Balance Test excursions. Inertial sensor testing will be captured during testing and analysed offline with MATLAB (2018b; MathWorks). Reach distances and the Y Balance Test will be normalised in relation to the individuals’ leg length, and the mean of three trials completed on each direction will be obtained. Movement control during the Y Balance Test will be quantified using the following variables: normalised reach distance and the SEn of the three axes of the gyroscope signal (x, y and z). SEn of the signal of length N=(x1, x2, x3, …, xn), will be calculated using the following formula:

Sample Entropy = −log (A/B)

Our interpretation of SEn scores is underpinned by key theories in the optimal variability during human motor performance, described by Stergiou and Decker, where a low SEn score indicates more regular and less complex movement control during the Y Balance Test reach excursions, while a higher SEn score indicates a higher degree of movement irregularity/complexity.^39^

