### Statistical analysis

All data will be analysed using the Statistical Package of Social Sciences (SPSS) (V.26; SPSS).

Baseline outcomes (concussion history, Y Balance, PLRM) will be summarised using means and SDs for scale variables and frequencies and percentages for nominal variables. We will use histograms to examine the frequency distributions of scale variables, and where normality is assumed, we will use independent t-tests to compare baseline data (PCSS, Y Balance, PLRM), with players categorised into two groups based on self-reported history of concussion in the last 12 months (no concussion in the last 12 months or concussion within the last 12 months). To avoid bias, researchers will be blinded to group title (ie, history of concussion vs no history of concussion). The threshold for statistical significance will p<0.01 for all tests. We will also present mean differences (95% CIs) between groups for scale outcome data.

SRCs occurring throughout the 2022/23 playing season will be summarised using counts (n, %). Time to SRC event will be plotted using survival curves, with participants censored at the end of the playing season. Serial outcome data (PCSS, Y Balance, PLRM, PFAB-TBI) will be measured at 72 hours, 7 days, 14 days, 23 days, 90 days, 180 days and 365 days postconcussion; we will initially determine the number (%) of participants that had returned to baseline at each time point. We will also examine the growth/response curves for each participant, as well as compare curves between known groups; sex and concussion history. As the shape of the time-response curve is uncertain and may vary across each outcome variable, we will calculate summary measures for each participant based on either the peak value, the time to return to baseline or the area under the curve. Area under the curve will be calculated using the trapezium rule (by adding the areas under the graph between each pair of consecutive observations). The most suitable summary measure will be used in the calculation of a median score (IQRs) for each outcome variable. Between-group comparisons will also be made, comparing curves across two known groups, for example, males/females and history of concussion/no history.

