### Sample size

We aim to enrol 250 participants at baseline. This figure allows for a 20% loss to follow-up over the entire study and assumes a 10% concussion prevalence over a single playing season. This will generate recovery data from approximately 20 participants presenting with a new concussion. Recruitment will be stratified to include equal numbers of male and female participants (n=125 males; n=125 females).

A sample of 250 participants would also provide sufficient power for detecting baseline difference in sensorimotor function. Our previous research^24^ had a medium effect standardised mean difference (SMD) 0.5 between adolescents with a history of concussion to those with no history for sensorimotor function with SDs of 0.22 units (SEn). Based on an alpha level of 1%, n=180 participants would provide 90% power for detecting a medium effect difference in SEn between groups at baseline.

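### The sample size powers one SEn comparison at 1%, but SEn is several variables and none is named to carry the claim

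*Protocol article*

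**What the plan says.** All places are in the protocol article.

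- **Sample size.** Earlier work is cited for a "medium effect standardised mean difference (SMD) 0.5 between adolescents with a history of concussion to those with no history", with an SD of 0.22 SEn units. From this the section concludes: "Based on an alpha level of 1%, n=180 participants would provide 90% power for detecting a medium effect difference in SEn between groups". SEn is treated as one quantity with one effect size and one SD.
- **Physical assessment.** The Y Balance Test has three reach directions, and trials are averaged within each direction. The variables listed are "normalised reach distance and the SEn of the three axes of the gyroscope signal (x, y and z". No average across axes, directions or legs is defined.
- **Statistical analysis.** Y Balance, the pupil metrics and PCSS are compared at baseline by t-test, with "players categorised into two groups based on self-reported history of concussion in the last 12 months". The rule for judging them is: "The threshold for statistical significance will p<0.01 for all tests".
- **Outcome measures** and **Aims.** No outcome is ranked above another. The first objective asks about sensorimotor and oculomotor outcomes as domains.

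**The concern.** The sample size describes one test. The analysis contains several tests of the same construct, all with equal standing. The SMD of 0.5 and SD of 0.22 can belong to only one of those SEn variables or to some average of them, and the article does not say which.

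The conclusion in view is at domain level, namely that sensorimotor function differs at baseline by concussion history. With no SEn variable singled out, whichever axis or direction reaches p<0.01 could be presented afterwards as the powered result. The 1% and the 90% would then be attached to a claim they do not describe, and a reader could not tell the powered test from the others.

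**Working it through.** **Inputs from the article.** Alpha 0.01 per test; SMD 0.5 (0.5 × 0.22 = 0.11 SEn units); stated n = 180 and power 90%; planned enrolment 250; three axes; three reach directions.

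**Assumptions.** Two-sided tests and equal history groups for the power check, because the article states neither. The correlation between SEn variables is not given, so a range is shown.

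**Step 1: the plan's own figure.** With the normal approximation, n per group = 2(z₀.₉₉₅ + z₀.₉₀)² / SMD² = 2(2.576 + 1.282)² / 0.25, which rounds up to 120, or 240 in total. The exact t calculation gives 121 per group. The stated 180 does not reproduce:

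| Reading of 180 | Power |
|---|---|
| 180 in total, two-sided 1% | 78.2% (77.2% by exact t) |
| 180 in total, one-sided 1% | 84.8% |
| 180 per group, two-sided 1% | 98.5% |
| 180 in total, two-sided 5% | 91.8% |

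So even with one SEn variable fixed in advance, the 90% does not hold at 180 in total and 1%.

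**Step 2: how many SEn variables.** Three axes are stated outright. Crossing them with three directions gives 3 × 3 = 9. The second count is inferred from averaging within direction and from the absence of any pooling rule.

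**Step 3: chance of at least one false positive.** If there is no true difference and the tests are independent, the chance is 1 − 0.99^k:

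- k = 3: 1 − 0.9703 = 3.0%
- k = 9: 1 − 0.9135 = 8.6%

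Whatever the correlation, the chance cannot exceed k × 1%, that is 3% and 9%.

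The SEn values come from one sensor during one task, so positive correlation is likely. Simulating equicorrelated normal test statistics (1,000,000 draws, two-sided 1% each) gives:

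| Common correlation | 3 variables | 9 variables |
|---|---|---|
| 0 (formula) | 3.0% | 8.6% |
| 0.3 | 2.9% | 7.9% |
| 0.5 | 2.7% | 6.7% |
| 0.7 | 2.4% | 5.1% |
| 0.9 | 1.8% | 3.0% |

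The rate stays above 1% throughout, including at the smallest count the text allows.

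**Step 4: the price of adjusting instead of choosing.** Holding 1% over nine SEn tests by Bonferroni means 0.01/9 = 0.00111 each. At 90% power per test (two-sided, equal groups, SMD 0.5), that needs 332 participants in total. With 250, power per test is 75.6%. Naming one variable keeps alpha at 1% and the requirement at 240.

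**The case against.** The strongest reply is that the article never promises 1% across a set of tests. It sets a per-test threshold, already stricter than 5%, and that threshold is valid for each test. This stands. A reader might infer that the plan states a family-wise 1% rate and breaks it, but the text does not support that. The point is limited to a domain-level claim that any one SEn variable could carry.

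Second, nine variables is an inference. The sentence on averaging within direction opens with reach distances, and SEn appears only in the next sentence. This also stands, so the result is given for three variables as well.

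Third, a reader might count the two legs separately, or add the pupil metrics and PCSS, and arrive at a much larger error rate. The article does not say that legs are analysed separately. A chance finding on a pupil or symptom measure cannot support a sensorimotor conclusion. Those counts do not belong here.

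Fourth, this is a condensed article. The choice of axis, direction and limb may be in a fuller plan or in the cited testing protocol, neither of which is available here. That would excuse a missing detail. It does not fully answer the point, because the article itself fixes alpha, power, SMD and SD on SEn while defining SEn as more than one variable.

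Last, recovery is the main aim, the baseline power is presented as an additional benefit of the sample, and mean differences with 95% intervals are promised. This limits the consequence but does not identify the powered test.

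**Conclusion.** The concern holds in a limited form. The 1% is correct for each test. It is not the error rate of a baseline sensorimotor claim that may rest on any SEn variable. That rate is about 1.8% to 3.0% with three variables and 3.0% to 8.6% with nine, for common correlations from 0.9 down to zero. These figures assume no true difference, two-sided tests and equal correlation between all variables. The inflation is modest because the threshold is strict, and it does not invalidate the study. It is worth correcting because the rule as written leaves the powered variable open until the data have been seen.

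The power figure is a separate defect. On two-sided tests and equal groups, 180 in total gives about 78%, and naming a variable does not repair that.

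**What to change.** Before analysis, add a sentence naming the one SEn variable (axis, reach direction and limb), or a defined average, to which the SMD of 0.5 and SD of 0.22 refer. Test it at 1% as the powered baseline comparison. Report the remaining SEn, reach, pupil and PCSS comparisons as secondary estimates with intervals. With one variable named, the powered claim needs no multiplicity adjustment.

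Correct the power statement at the same time, stating the sidedness and the expected split between history groups. Two-sided with equal groups, 90% power needs 240 in total.

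Data collection does not change. The cost is that no other SEn variable can afterwards carry the powered claim.

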## Introduction

Sport-related concussion (SRC) is a complex pathophysiological process affecting the brain induced by traumatic biomechanical forces.^1^ Paediatric visits to emergency departments for concussion and minor head injuries have doubled in the USA in recent years.^2^ Many concussions occur during contact and collision sports like rugby union. The rate of concussion in professional rugby union is estimated at 21.5 per 1000 game hours.^3^ Incidence is also high in adolescent rugby with estimates of an incidence of 6.1 concussions per 1000 game hours, which is equivalent to 3 concussions per team per season.^4^

SRC can affect a variety of subsystems, including oculomotor,^5^ somatosensory,^6^ vestibular systems,^7^ with disturbances to cognition,^1^ mood^8^ and biomarker profile.^9^ Clinical recovery after an SRC can typically take between 10 days and 14 days in adults^1^ and up to 4 weeks in adolescents.^10^ It is recommended adolescent athletes undergo a battery of tests postconcussion,^1 11–13^ including the Sports Concussion Assessment Tool.^14^ While research into the recovery from concussion in adolescents is growing, most research focuses primarily on neurocognitive functioning, subjective and symptom-based outcomes.^15–17^ Few prospective studies examine sensorimotor or oculomotor function postconcussion, and the natural progression of recovery for these subsystems is poorly understood.

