SRCs in adolescents remain a great concern due to the uncertainty surrounding their pathophysiology, the potential moderating effects of cognitive maturation and poorly understood recovery. New technologies (eg, wearable inertial sensors and pupillometry) can enhance the existing battery of assessment, providing more objective, natural recovery data for key subsystems (oculomotor, sensorimotor). Sex differences exist throughout development, but there is a dearth of prospective research involving adolescent females who sustain an SRC and recovery. There is a need for longitudinal research in SRC as many neurophysiological deficits persist beyond the point of clinical symptom resolution.^31–35^

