### SRC events

SRC prevalence will be recorded over a single playing season (2022/23). SRC definition will follow the criteria set out by the Zurich Consensus Statement on Concussion in Sport^1^; that is, a direct blow to the head, face, neck or elsewhere on the body with an impulsive force transmitted to the head resulting in one or more of the symptoms in one or more of the following clinical domains (which may or may not have involved loss of consciousness): somatic, cognitive, emotional/behavioural and sleep disturbance. All SRCs must be verified by a medical professional within 48 hours of the injury. When a participant is diagnosed with a concussion, the designated person at each school/club (data champion) will be responsible for contacting the primary researcher ([name]). [name] will maintain weekly contact with the data champion, sending study reminders via text message or a follow-up phone call. The following information will be inputted for each concussion: date of injury, reporter/person making the diagnosis, site where diagnosis was made, cause of injury (phase of play, direct vs indirect), time to first symptoms and nature of first symptoms.

In the event of an SRC, all outcome measures will be reassessed by the primary researcher after 3 days, 7 days, 14 days and 21 days and 3 months, 6 months and 12 months. Dates of return to training and return to play will be self-reported by the participant or coach. Return to play dates will be cross referenced with the official team lists registered with Ulster Rugby. The researchers involved in this study will have no influence on the return to training or return to play decisions; these decisions will remain external to the current project. Participants will be asked on return visits as to whether they have experienced any treatment or intervention relating to their concussion between visits. Any and all interventions undertaken by individuals will be considered and reported when analysing the results.

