In an exploratory analysis, we will use logistic regression to examine the association between demographic variables (age, sex, previous injury) and recovery at 23-day follow-up. We will run separate models for each outcome measure (PCSS, Y Balance, PLRM, PFAB-TBI). Our previous research^4^ found that 90% of adolescent rugby players return to sport at 23 days postconcussion; this is also the minimal convalesce for adolescent players postconcussion based on Irish Rugby Football Union and World Rugby guidance, which are built around the latest medical research and expert-based opinion.^46^ Full recovery will be defined as a return to baseline (preseason) values for each respective outcome. Initially, we will conduct a series of univariate analyses to determine whether any predictor variables are associated with recovery. Correlations among predictor variables will be calculated to screen for any strong colinearity (r>0.8). Predictors demonstrating a p value less than 0.10 on univariate testing will be entered into a multiple logistic regression analysis. The strength of the predictive model will be determined using R^2^, p values and ORs, with 95% CIs.

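### Time to return to baseline cannot be dated between the day-23 (or day-21) visit and day 90, so where that summary is chosen it should be handled and reported as an interval

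*Protocol article*

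**What the plan says.** Three statements in the protocol article matter here.

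- **Schedule.** The Statistical analysis section has serial outcomes "measured at 72 hours, 7 days, 14 days, 23 days, 90 days, 180 days and 365 days postconcussion", and the Abstract agrees. The SRC events section says that "all outcome measures will be reassessed by the primary researcher after 3 days, 7 days, 14 days and 21 days and 3 months, 6 months", with a last visit at 12 months; the Outcome measures section also gives day 21. Neither schedule has a visit between the fourth assessment and month 3.
- **Summary measure.** Each player's curve is to be reduced to one number, "based on either the peak value, the time to return to baseline or the area under the curve". Then: "The most suitable summary measure will be used in the calculation of a median score (IQRs) for each outcome variable".
- **Recovery.** "Full recovery will be defined as a return to baseline (preseason) values for each respective outcome". That can be observed only when the outcome is measured.

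The Introduction puts typical clinical recovery at "up to 4 weeks in adolescents" and adds that "many neurophysiological deficits persist beyond the point of clinical symptom resolution". For the area under the curve, the article states how to bridge consecutive visits ("by adding the areas under the graph between each pair of consecutive observations"). It gives no corresponding rule for time to return to baseline.

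**The concern.** A recovery time reported as a median with IQR looks like a measured duration. On this schedule it is known only to lie between two visits. Early on those visits are 4 to 9 days apart and this matters little. After the fourth visit the gap is more than nine weeks, and it contains the 4-week point that the article gives as the typical upper end of clinical recovery.

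The study's question is how long sensorimotor and pupil deficits last. If a visit day is reported as a recovery time, a player who recovered in week 4 or 5 appears as persisting to 3 months, although persistence to that point was not observed. Two groups whose true times differ by a few days either side of day 23 could appear to differ by 67 days.

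**Working it through.** **Inputs.** Visit days 3, 7, 14, 23, 90, 180, 365 (Statistical analysis), or day 21 as the fourth visit (Outcome measures, SRC events), with months 3, 6 and 12 taken as days 90, 180 and 365. Clinical recovery up to 4 weeks, so day 28 (Introduction). Enrolment 250, 20% loss, 10% concussed (Sample size).

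**Plan's own figure.** 250 × (1 − 0.20) × 0.10 = 20 concussed players. This reproduces the stated number.

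**Gaps.** Consecutive differences are 4, 7, 9, 67, 90 and 185 days. With day 21 the third and fourth become 7 and 69, so the critical gap is slightly longer.

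**One player, read at the first recovered visit.** Recorded day = first visit on or after the true day.

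- True day 24: recorded 90, 66 days late.
- True day 28: recorded 90, 90 − 28 = 62 days late (90/28 = 3.2 times the true value).
- True day 42: 48 days late. True day 60: 30 days late.
- With the day-21 schedule, a day-22 return is also recorded as 90, 68 days late.

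**Other ways of dating it.** A straight line from an excess h on day 23 to baseline on day 90, h × (1 − (t − 23)/67), reaches zero at t = 90, the same answer. The interval midpoint is (23 + 90)/2 = 56.5, which dates a day-28 return 28.5 days late. No rule can recover a date that was not observed.

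**Effect on the quartiles with 20 players.** If six are unrecovered at day 23, the 15th and 16th ordered values are both 90 or later, and so is the upper quartile. If eleven are unrecovered, the 10th and 11th values, and hence the median, are 90 or later. With exactly ten, the median averages 23 with the next value, giving 56.5 if that value is 90. Let p be the true proportion unrecovered at day 23 on one outcome, and X the number of the 20 unrecovered. Then P(X ≥ k) = Σ C(20, j) p^j (1 − p)^(20 − j), summed over j from k to 20:

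| p (assumed) | Expected of 20 | P(upper quartile at 90 or later), k = 6 | P(median at 90 or later), k = 11 |
|---|---|---|---|
| 10% | 2 | 1.1% | < 0.0001% |
| 20% | 4 | 19.6% | 0.06% |
| 30% | 6 | 58.4% | 1.7% |
| 40% | 8 | 87.4% | 12.8% |
| 50% | 10 | 97.9% | 41.2% |

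The article gives no value of p for any outcome. Its only day-23 figure is that 90% are back in sport, which would be p = 10% if it carried over.

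**Group difference.** True returns on days 22 and 24 differ by 2 days. Read at visits they are 23 and 90, a difference of 67.

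**The case against.** The strongest reply is that the faulty rule is not in the text. The article does not say that the first recovered visit will be used, and dating events between visits is detail that an article may leave to a fuller plan. That stands: a reader might infer that the authors have adopted visit-day dating, and the document does not show it. What remains is that the stated schedule cannot resolve the stated summary, whether the time is read at visits or interpolated to a baseline value on day 90.

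Second, a reader might infer that the study's headline median will be overstated several-fold. The article does not support this. Time to return is one of three candidate summaries and is nowhere called primary. The 4-week figure is a typical upper end for clinical recovery, not a limit, and not a figure for entropy or pupil metrics. The Introduction says that deficits outlast symptoms without saying for how long, so nothing places most recoveries just after day 23. If about 10% are unrecovered then, the median is safe and the upper quartile nearly so. Return to sport is, however, an imperfect proxy for return of each outcome to baseline, so larger proportions cannot be excluded.

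Third, the plan will first report the number and percentage back to baseline at each visit. This largely discloses the interval already. But a median of 90 days printed beside those percentages would still be read as a duration.

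Fourth, with complete visits, ordering players by interval gives the same ranks as ordering them by first recovered visit, so a rank test would not change. That is correct. The gain is in the reported median, quartiles and day differences, and in players who miss visits, a risk that the article's own limitations acknowledge.

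**Conclusion.** The point holds as a limited, conditional one. Under either schedule a return after the fourth visit and by day 90 can be located only within a 67- or 69-day interval. Presenting it as day 90 dates a day-28 recovery 62 days late. With about 20 concussed players the upper quartile is exposed first: about 1% probability of moving to 90 or later if 10% are truly unrecovered at day 23, 58% if 30% and 87% if 40%. The median is exposed only when about half or more are unrecovered.

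These figures rest on an assumed range for the proportion unrecovered, independent players, complete visits, and visit-day reading where time to return is the chosen summary. The day-23 logistic regression is not affected by this gap.

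**What to change.** Where time to return to baseline is the chosen summary, state that each player's time is interval-censored: after the last unrecovered visit (or the injury, if already recovered at the first visit) and up to the first recovered one, and right-censored if recovery is never seen. Estimate the distribution with a Turnbull or similar interval-censored method. Report the interval that contains the median and each quartile, for example between day 23 and day 90. Do not report a visit day, or a between-group difference in visit days, as a recovery time.

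Reconcile the day-21 and day-23 statements for the fourth assessment, because that day sets the lower end of the critical interval.

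No visit is added. The cost is a few sentences and perhaps a short script outside SPSS, which the article names for all analyses. The downside is that recovery time is stated as a range, which looks less precise but matches what was observed.

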The sensorimotor system plays a central role in regulating postural control and balance. Retrospective data suggest that 30% of adolescents presenting with concussion have vestibulo-ocular deficits in the acute postinjury period.^18^ Adolescent players with acute vestibular dysfunction also have worse prognosis^19^ with a fourfold greater risk of developing postconcussion syndrome.^20^ Clinical assessment of sensorimotor function is based on balance tests such as balance error scoring system (BESS), dynamic tasks like the Y Balance Test, or a 3-metre walk test. However, these traditional tests are scored subjectively, and lack the responsiveness needed to detect small but important deficits in sensorimotor performance. Adding wearable sensor technology to traditional balance tests can improve their accuracy, allowing researchers to quantify subclinical balance deficits. Previous research has shown that sensor-based instrumentation of the Y Balance Test provides a reliable and valid measure of movement control,^21 22^ and is more responsive than the traditional reach distance scoring method.^23^ In a study of adolescent rugby union athletes aged 14–18 years, those with a history of concussion had poorer dynamic balance (high sample entropy (SEn)) during Y Balance Tests compared with non-concussed controls.^24^ There is evidence of Quantified Y Balance Tests predictive validity, and elite male rugby union players presenting with greater irregularity in their Y Balance Test movement control were three times more likely to sustain a concussion than the players with more regular Y Balance Test movement control.^23^

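### Recovery is not conditioned on prior worsening, so for Y Balance, pupillary and fear-avoidance outcomes the recovery percentages, times to return and day-23 models mix never-impaired with recovered players

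*Protocol article*

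**What the plan says.** The Statistical analysis section of the protocol article gives one definition: "Full recovery will be defined as a return to baseline (preseason) values for each respective outcome". It is used in three places.

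- **Percentages.** For PCSS, Y Balance, the pupillary light reflex (PLR) and PFAB-TBI, "we will initially determine the number (%) of participants that had returned to baseline at each time point". The outcomes "will be measured at 72 hours, 7 days, 14 days, 23 days, 90 days, 180 days and 365 days postconcussion".
- **Summary measures.** Each player's curve is reduced to one number, "based on either the peak value, the time to return to baseline or the area under the curve".
- **Logistic models.** An exploratory analysis will "examine the association between demographic variables (age, sex, previous injury) and recovery at 23-day follow-up", with a separate model for each outcome.

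Entry to the recovery cohort is set in the SRC events section. A concussion is a blow "resulting in one or more of the symptoms in one or more of the following clinical domains", the domains being somatic, cognitive, emotional/behavioural and sleep. No change in balance, pupil response or fear-avoidance is needed.

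The only figure in the document for how often a subsystem is affected is in the Introduction: "Retrospective data suggest that 30% of adolescents presenting with concussion have vestibulo-ocular deficits in the acute postinjury period".

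**The concern.** Entry is decided on symptoms, while recovery is decided outcome by outcome against the player's own preseason value. For an outcome the concussion did not touch, the state at entry and the recovered state can be the same. Such a player can count towards the percentage returned from the first visit, receive an early time to return, and be coded as recovered in the day-23 model.

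The study aims to describe recovery of each subsystem and to compare it by sex and concussion history. If two groups differ in how many players are affected but not in how well affected players recover, the plan will show a difference in recovery. The reader could not tell from the recovery percentage or the odds ratio which of the two had occurred.

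**Working it through.** **Inputs from the protocol article.** Sample size section: 250 enrolled, 20% loss, 10% concussed, SD of sample entropy (SEn) 0.22, standardised difference 0.5. Introduction: 30% with acute vestibulo-ocular deficits.

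**Assumed inputs.** The impaired share p for each outcome, the recovery r among impaired players, and test-retest ICC from 0.7 to 0.9. The document gives none of these for Y Balance, PLR or PFAB-TBI.

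**Step 1, the plan's denominator.** 250 × (1-0.20) × 0.10 = 20. The stated figure of about 20 concussed players reproduces.

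**Step 2, effect without measurement error.** Never-impaired players contribute 1-p and recovered players p×r.

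- Reported rate = (1-p) + p×r.
- Never-impaired share of counted recoveries = (1-p) / [(1-p) + p×r].

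| p | r | Reported rate | Rate among impaired | Never-impaired share of counted recoveries |
|---|---|---|---|---|
| 0.30 | 0.5 | 0.70 + 0.15 = 85% | 50% | 82% |
| 0.30 | 0.9 | 0.70 + 0.27 = 97% | 90% | 72% |
| 0.50 | 0.5 | 0.50 + 0.25 = 75% | 50% | 67% |
| 0.70 | 0.5 | 0.30 + 0.35 = 65% | 50% | 46% |
| 0.90 | 0.5 | 0.10 + 0.45 = 55% | 50% | 18% |
| 1.00 | 0.5 | 0.00 + 0.50 = 50% | 50% | 0% |

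At p=0.30 and r=0.5, 14 of 20 never worsened and 3 of the 6 impaired recovered, so 17 of 20 are counted. Never-impaired players exceed half of counted recoveries only if p < 1/(1+r), that is below 0.67 for r=0.5 and below 0.53 for r=0.9.

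**Step 3, effect on a group comparison.** Let r=0.5 in both groups, with 30% impaired in one and 50% in the other (illustrative values). The reported rates are 1 - 0.3×0.5 = 85% and 1 - 0.5×0.5 = 75%. The odds ratio is (0.85/0.15) / (0.75/0.25) = 1.89, with identical recovery among impaired players.

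**Step 4, effect with measurement error.** The document gives no direction or tolerance for a return. Suppose a strict rule of at or better than the preseason value, with independent errors at both visits. A never-impaired player then meets it about 50% of the time at any one visit, whatever the ICC. Simulation with r=0.7, 400,000 players, and deficits of 0.5 or 1 SD (0.11 or 0.22 SEn units) at p=0.30, 1 SD at p=0.70, gives:

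- Never-impaired share of counted recoveries: 73-77% at p=0.30 and 36-38% at p=0.70.
- Reported rate for a 1 SD deficit: about 46% at p=0.30 and 40-41% at p=0.70, again with the same r.

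Error under a strict rule therefore lowers the reported rate, which here falls below r. The mixing and the artificial group difference remain.

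**The case against.** Several points on the other side stand in part.

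- **The word return implies a departure.** The text is silent on players who never departed; it does not state that they count as recovered. A condensed article may also leave coding detail to a fuller document. But the article does fix the definition and the outcome of the models, and neither contains a worsening condition.
- **The plan would show some of this anyway.** The 72-hour count, individual response curves, peak value and area under the curve would reveal part of the non-impairment, the return count is only the initial summary, and the day-23 models are exploratory. All true, but none of it enters the definition of recovery.
- **Stronger readings are tempting.** A reader might infer that any player at or better than baseline counts, and that the recovery rate mostly measures who was unaffected. The document supports neither. The direction is not stated, and under a strict rule only about half of never-impaired players qualify at one visit. *Mostly* depends on carrying a retrospective vestibulo-ocular figure over to other outcomes, while the Introduction also calls oculomotor dysfunction common after concussion and reports differences on eight of nine PLR metrics.
- **A 3-day median time to return.** A reader might infer this from 70% being unaffected. It holds only without measurement error. With error, p=0.30 and a strict rule, 35-43% of all players meet the rule at day 3.
- **Restricting the denominator brings its own error.** Label players impaired if they exceed a one-sided 95% limit at day 3 or day 7, with p=0.30, deficits of 0.11-0.22 units and ICC 0.7-0.9. Then 19-44% of those labelled impaired never were, 14-74% of the truly impaired are missed, and about 3-6 of 20 players remain. This objection stands and limits the fix.

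**Conclusion.** The concern holds for Y Balance, PLR and PFAB-TBI: as defined, recovery does not distinguish a player who was never impaired from one who was impaired and returned. This affects the percentages, the time to return and the day-23 models. PCSS is largely exempt, since every case has symptoms at injury, although some may resolve before the first visit.

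The size depends on the impaired share, which the document does not give for these outcomes. Without measurement error and at r=0.5, the overstatement is 35 percentage points if the 30% figure carries over and 5 points if 90% are impaired. With error, the amount depends on the rule chosen for a return. The direction of the group artefact does not change: at equal r, the group with fewer impaired players appears to recover better.

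Being at baseline on day 23 is a legitimate quantity for all concussed players. What the plan cannot support is calling it recovery and reading its odds ratios as predictors of recovery.

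**What to change.** For each sensorimotor, oculomotor and fear-avoidance outcome:

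1. Prespecify the direction of worsening and a measurement-error limit. From the visits already planned, report the number (%) who worsened from preseason beyond that limit.
2. Beside the all-player count, show a three-way table: not impaired, impaired and returned, impaired and not returned.
3. Label the all-player day-23 outcome as *at baseline at day 23*, and state that its odds ratios are not interpreted as predictors of recovery.
4. Give the percentage and time to return among impaired players as a descriptive supplementary result only, not as a replacement denominator or a model outcome.

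The cost is a few table rows and some wording, with no new visits. The measurement-error limit has to be sourced, since the article gives none. The impaired subgroup may be 6 of 20 or fewer, so its estimates will be imprecise. Early visits are noisy and impairment will be misclassified in both directions; the report should say so.
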